### Data analysis

We will compare the following measurements between the Clinical Decision Aid Group and the current practice only Control Group: baseline characteristics, perceptions and attitudes toward decision-making in the clinic visit, medication initiation (e.g., statins or beta blockers for cardioprotection), cardiovascular lab testing obtained, physical activity pursued (based on survey responses), cardiovascular imaging tests ordered or recommended for surveillance. We will also analyze data using qualitative descriptive statistics for focus group results from patients and clinicians in the Clinical Decision Aid Group.

Scores will be calculated for individual survey questions, with a higher number indicating a more favorable response. The randomization groups will be considered as the independent variables and survey scores, as well as short-term outcome measures, such as cardiovascular medication initiation and imaging parameters, and lab test results if applicable, as the dependent variables. Survey scores, imaging parameters, medication use, and lab tests if applicable, will be compared between the group of patients that use the clinical decision aid (Clinical Decision Aid Group) and the group of patients that do not use the clinical decision aid (Control Group) at single visits (baseline, three months, six months). Additionally, survey scores for information seeking and sharing, as well as imaging parameters and medication use, and lab tests if indicated, will also be compared between the Clinical Decision Aid Group and the Control Group between visits. Thus, changes over time in the Information Seeking and Sharing survey responses, imaging parameters, medication use, and lab tests if results applicable, will be investigated. We will assess whether survey responses, imaging parameters, medication use, and lab tests if applicable, differ by study group (Clinical Decision Aid Group versus Control Group) or by risk-stratified patient similarity cluster. We may also pursue subgroup analyses to compare clinical decision aid and Control Group results within each patient similarity risk cluster, between races, or by sex.

Simple group comparisons will be made using the chi-square or Fisher’s exact test as appropriate for binary survey score variables. Logistic regression will also be used to estimate the effect of the randomized group on the binary score for each survey question, to allow us to adjust data for the following baseline socioeconomic demographics: age, sex, and level of education if known. These demographic characteristics will also be investigated as potential predictors using multivariate analyses, for survey questions or short-term outcomes with results significantly different between the two randomized groups. Continuous variables will be expressed as mean with standard deviation, whereas dichotomous variables will be expressed as percentages. For continuous characteristics or outcomes, Wilcoxon rank sum test or two-sample t-test will be used as appropriate. Statistical data will be expressed as odds ratio with confidence interval or mean with standard error. Statistical significance will be accepted as *P*-value of < 0.05.

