### Clinical visits and clinical decision aid intervention

Patients in the study will meet with study cardiologists in either a virtual or in-person clinically indicated visit, with technical support and training provided by the study team as needed. For those in the Clinical Decision Aid Group, their personalized risk output from the artificial intelligence algorithms will be organized in a meaningful and user-friendly way, using customized pictographs visually representing personalized and precise patient risk in the clinical decision aid (Fig. 3). This will be juxtaposed with suggestions for medication use and imaging based on existing guidelines, expert recommendations, and society scientific statements (from Fig. 2).

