### Follow-up clinic visits

Follow-up clinic visits may be pursued as clinically indicated. Patients in the Clinical Decision Aid Group may again use the clinical decision aid, which would be an updated version incorporating some of the focus group feedback and suggestions. In addition, study participants in the Control Group will receive their risk group information at the end of the study if desired and can review again at that time with their clinicians the preventive steps they have taken for heart health.

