### Secondary endpoints

Survey responses will be reviewed to determine the impact of the use of the clinical decision aid, in addition to current practice, on cancer survivors’ perceptions of the tool and heart health-related behaviors. The percentages of favorable survey responses and scoring tool results in the patient group using the clinical decision aid will be compared to results from the patient group that does not use the clinical decision aid. A high score will indicate favorable responses for a particular survey, demonstrating favorable perception of the tool regarding the survey topic. We anticipate ≥ 80% of survey questions scored favorably by the group of patients who use the clinical decision aid, with scores the same or higher than the group without the clinical decision aid [39].

Clinically indicated lab values such as troponin, NT-pro-BNP, potassium, and lipid panel, along with BMI, will also be reviewed.

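### Lab results are tested between arms at three and six months only in patients who happened to be tested, and the aid may change who is tested

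*Protocol article*

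**What the plan says.** All references are to the protocol article.

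- **Data analysis.** The randomised group is the independent variable. Lab test results, where applicable, are among the dependent variables. "Survey scores, imaging parameters, medication use, and lab tests if applicable, will be compared" between the arms, "at single visits (baseline, three months, six months"). In addition, "lab tests if indicated, will also be compared between the Clinical Decision Aid Group and the Control Group between visits", so changes over time are also examined by arm.
- **Data analysis, tests.** "For continuous characteristics or outcomes, Wilcoxon rank sum test or two-sample t-test will be used as appropriate". Significance is declared at P below 0.05.
- **Follow-up clinic visits.** "Follow-up clinic visits may be pursued as clinically indicated". No three- or six-month visit is set for everyone.
- **Secondary endpoints.** "Clinically indicated lab values such as troponin, NT-pro-BNP, potassium, and lipid panel, along with BMI, will also be reviewed".
- **Whether testing happened is itself an outcome.** Data analysis lists "cardiovascular lab testing obtained" among the measurements compared between arms. Table 2 lists lab testing obtained as a secondary outcome.
- **What the aid shows.** Under Clinical visits and clinical decision aid intervention, the aid group receives a personalised risk display. "This will be juxtaposed with suggestions for medication use and imaging based on existing guidelines" and other recommendations.
- **Primary endpoints.** Chart review of medication use and imaging patterns is done for all patients at three and six months.

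**The concern.** A between-arm test is protected by randomisation only if the outcome is obtained in the randomised patients, or is missing for reasons unrelated to the arm. Here a troponin, NT-pro-BNP, potassium or lipid value exists only if a clinician saw a reason to measure it after randomisation. In one arm the clinician decides with a risk display on screen. In the other the clinician does not. If the display lowers the threshold for testing, the aid arm's tested group takes in patients with less clinical need, and its mean can move with no change in anyone's health. Comparing changes between visits narrows the group further, to patients with a value at both times.

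A lower mean biomarker in the aid arm with P < 0.05 would be easy to read as a benefit. The more the aid changes testing, the larger the distortion. Adjusting for age, sex and education, which the Data analysis section plans for the survey-score models, would not by itself remove it, because the selection runs through clinical need.

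**Working it through.** **1. The plan's own figure.** The article gives no power or precision for the lab comparisons. Its one sample-size calculation concerns the primary endpoint, 40% against 60% at 80% power. With the pooled two-sided formula:

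n = [1.960·√(2·0.5·0.5) + 0.8416·√(0.4·0.6 + 0.6·0.4)]² / 0.2² = (1.3859 + 0.5831)² / 0.04 = 96.9, so 97 per group.

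The stated 97 is reproduced, and this point does not change it.

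**2. Who contributes to each comparison.**

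| Outcome | Defined for | Affected? |
|---|---|---|
| Primary endpoint; medication prescribed, imaging ordered or obtained (yes/no) | All patients, by chart review at three and six months | No |
| Lab testing obtained (yes/no) | All patients: an absent test counts as no | No |
| Lab results | Patients tested because clinically indicated | Yes |
| Imaging parameters | Undefined: all patients if occurrence, imaged patients if measured values | Only if measured values |
| Survey scores | All participants are asked; the three- and six-month timing is tied to visits that are not guaranteed | Unclear; wording to be reconciled |

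**3. Illustration of size.** The article gives neither testing rates nor the correlation between need and value, so every input here is an assumption. The 40% and 60% below are testing fractions, not the consistency rates of the sample-size section.

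Model: each patient has a standard normal need for testing. The lab value has SD 1 and correlation ρ with need, and there is no treatment effect. A fraction p is tested, namely those with the greatest need. With z the standard normal quantile at 1 − p and φ the normal density:

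- mean need among the tested: m(p) = φ(z)/p
- spurious difference: d = ρ·[m(p aid) − m(p control)]
- variance of the value among the tested: v(p) = 1 − ρ²·m(p)·[m(p) − z]
- SE = √[v(p control)/(100·p control) + v(p aid)/(100·p aid)], with 100 patients per arm
- false-positive rate = Φ(−1.96 − d/SE) + 1 − Φ(1.96 − d/SE)

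For 40% against 60% tested, φ(0.2533) = 0.3863, so m(0.4) = 0.966 and m(0.6) = 0.644, a difference of −0.322.

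- ρ = 0.2: d = −0.064. v = 0.973 and 0.977. SE = √(0.973/40 + 0.977/60) = 0.201. False-positive rate 6.2%.
- ρ = 0.6: d = −0.193. v = 0.752 and 0.792. SE = √(0.752/40 + 0.792/60) = 0.179. False-positive rate 19%.

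Other cases (spurious difference in SD; false-positive rate):

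| Tested, control vs aid | ρ = 0.2 | ρ = 0.3 | ρ = 0.5 |
|---|---|---|---|
| 40% vs 40% | 0; 5% | 0; 5% | 0; 5% |
| 40% vs 50% | −0.03; 5.3% | −0.05; 5.7% | −0.08; 7.2% |
| 40% vs 60% | −0.06; 6.2% | −0.10; 7.8% | −0.16; 13.8% |
| 40% vs 85% | −0.14; 11.3% | −0.21; 19.9% | −0.35; 49.7% |

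**4. Loss of precision.** The difference detectable at 80% power is (1.960 + 0.8416)·√(1/n₁ + 1/n₂). This is 0.40 SD for 100 against 100 and 0.57 SD for 40 against 60.

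**The case against.** Much of the case against a broader criticism is sound.

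- **Surveys.** A reader might infer that survey scores come only from patients who return. The article does not say so. It asks study participants in general to complete surveys, and the Follow-up clinic visits section does not mention surveys. The word visits in the Data analysis section may simply mean time points: the same sentence covers medication use, which chart review collects for everyone at three and six months. What stands is that the wording ties survey comparisons to visits that are not scheduled for all.
- **Imaging.** A reader might infer that measured imaging values are compared. The term is undefined, and elsewhere the imaging outcomes are occurrences: Table 2 lists imaging recently obtained and imaging ordered, and the Discussion speaks of utilization. On that reading, chart review covers every patient and there is no selection.
- **The right comparison is already planned.** Data analysis and Table 2 include whether lab testing was obtained, which is a sound randomised comparison. The plan errs only in also testing the values.
- **Labs are peripheral.** They are hedged throughout and play no part in the success rule, the primary endpoint or the sample size. The aid is described as suggesting medication and imaging, not labs, so an effect on lab testing is plausible but not documented.

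One could add that the analysis set and missing-data handling belong in the analysis plan. That does not answer the lab point. The article itself fixes an inferential comparison of values that were never scheduled for collection.

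**Conclusion.** The point holds for lab results, and for imaging measurements if that is what the undefined term means. These values are tested between arms only in patients selected after randomisation, by a process the aid may influence, and the result should not be read as a treatment effect.

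It does not reach the primary endpoint, the yes/no outcomes or the sample size. The documents do not establish that the surveys are restricted to returners; there the need is to reconcile the text.

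The size cannot be derived from the documents. At 40% against 60% tested and a correlation of 0.2 to 0.6, the spurious difference is about 0.06 to 0.19 SD and the false-positive rate 6% to 19%. Under the same model it is zero when testing is equal across arms. The direction also rests on the assumption that extra testing reaches patients with less need. This is a secondary-outcome problem, worth correcting because the correction is cheap and its data-collection part must be in place before follow-up.

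**What to change.** 1. Keep the already planned comparison of labs and imaging obtained or ordered as the between-arm test, over all randomised patients. State that lab testing is recorded in the same three- and six-month chart review, with no test counted as no.
2. Report measured lab values, and any imaging measurements, descriptively by arm with the number tested and without p-values. Say what imaging parameters means.
3. Reconcile the three- and six-month comparisons in Data analysis with the Follow-up clinic visits section. Collect surveys from every randomised patient at fixed three- and six-month dates, whether or not a visit takes place, and compare the arms on that basis.

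Cost: changes of wording, survey mailings at two dates, and the loss of p-values for lab values. No further patients, visits or tests are needed.

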***Pre-Existing Cardiovascular-Related Medications***
*Patient already on ACE Inhibitor*
*Patient already on ARB*
*Patient already on Beta Blocker*
*Patient already on Statin*
*Patient already on Other Cardiovascular Medications*
*Patient already on Antidiabetic Medication*

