### Focus groups

As part of an exploratory study, a total of 20 patients in the Clinical Decision Aid Group and all the study physicians will attend two patient or physician focus group sessions, respectively. The focus groups will discuss the virtual clinical decision aid interface and how to improve it. Treating physicians will meet separately from patients in their own focus groups. The first will be held a week after the initial visit and the second held a week after a clinically indicated follow-up visit when applicable. Focus groups will be run by our qualitative research collaborators who will facilitate discussions about the user experience, to obtain critical feedback on the virtual clinical decision aid interface. The expectations for these focus group sessions are to help our study team further develop and improve the clinical decision aid interface to fit the needs of patients and their clinicians.

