### Primary endpoints

Chart reviews will also be completed for all patients to assess medication use and imaging patterns in accordance with cardio-oncology recommendations at three and six months after the baseline clinic visit, as the primary endpoints.

If the patient chooses not to or is unable to pursue the recommendations suggested by the clinical decision aid as discussed by the physician, this would be noted in the chart. Therefore, if the physician offers the recommendation, this will be considered consistent with the society statements, even if the patient chooses not to follow the recommendation. An adjudication committee of 3 people may be established to decide what is considered consistent with evidence-based recommendations. If 2 of 3 people agree, that would be considered consistent with evidence-based recommendations.

Success will be determined by ≥ 85% of clinic visits using the clinical decision aid resulting in pursuit of medication use and cardiac imaging surveillance patterns commensurate with recommendations specific to cancer survivors, with overall rates the same or higher than the group without the clinical decision aid, as well as overall favorable patient and physician focus group comments and survey responses.

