### Statistical methods

#### Sample size and power analysis

Assuming 40% consistency with evidence-based recommendations at baseline for both groups [18, 20, 40], we will consider clinical significance at a 50% increase from baseline, which corresponds to 60% consistency with the recommendations. To go from 40% at baseline to 60% in the intervention arm of the trial (i.e., Clinical Decision Aid group) with 80% power requires 97 patients in each group, or 194 total patients. We may be powered to detect such a clinically reasonable change in the primary endpoint. Although we may be powered for this modest change, we could also consider a greater increase from baseline. To go from 40 to 85% with 80% power requires 17 patients in each group, or 34 total patients. We would also be powered for this, but this increase may not be reasonably obtainable.

In this feasibility study, the total number of patients will be limited to 200. One cohort of 100 patients will have clinic visits with current practice plus the clinical decision aid. The other cohort of 100 patients will have clinic visits with current practice alone. This should allow for capturing a variety of cancers and include ethnic minorities in each group.

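### The baseline visit is also the first visit with the aid, so the additional change analysis can remove part or all of the aid's effect unless its baseline values are taken before the aid is shown

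*Protocol article*

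**What the plan says.** All references are to the protocol article.

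- **Primary endpoints.** Chart reviews of medication use and imaging are done "at three and six months after the baseline clinic visit, as the primary endpoints". Follow-up time is therefore counted from the baseline clinic visit.
- **Clinical visits and clinical decision aid intervention.** "Patients in the study will meet with study cardiologists in either a virtual or in-person clinically indicated visit"; the aid arm sees its risk output and care suggestions there. No earlier study visit without the aid is described.
- **Focus groups.** Of the two sessions about the aid's interface, "The first will be held a week after the initial visit".
- **Follow-up clinic visits.** These take place only if clinically indicated, and "Patients in the Clinical Decision Aid Group may again use the clinical decision aid" at them.
- **Data analysis.** Survey scores, imaging, medication use and laboratory tests are compared between aid users and non-users "at single visits (baseline, three months, six months"). A further comparison between visits is then announced, so that "changes over time in the Information Seeking and Sharing survey responses, imaging parameters, medication use, and lab tests if results applicable, will be investigated".
- **Sample size and power analysis.** The calculation starts from "Assuming 40% consistency with evidence-based recommendations at baseline for both groups" and sets 60% as the target in the aid arm.
- **Table 2.** It has a block headed "Pre-Existing Cardiovascular-Related Medications" and one for imaging recently obtained, each separate from the blocks for medications and imaging ordered.

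**The concern.** Baseline carries two meanings. In the sample-size section it is the state before the intervention, the same in both arms. In the analysis section it is a clinic visit at which outcomes are compared, and that visit is where the aid arm first meets the aid.

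The aid is meant to act during the consultation, when clinician and patient decide on medication and imaging. Under Primary endpoints, a recommendation counts as consistent once the physician offers it, even if the patient declines. A sizeable part of any effect could therefore appear at the first visit. If the reference value for change already contains that part, the change comparison measures only what happens afterwards. The same trial could then show a difference at each single visit and little or none in change, and a reader could take the second result as evidence against the aid.

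**Working it through.** **Step 1. Is the baseline visit the first-use visit?** The article does not say so in one sentence, but three statements lead there. Use at follow-up is described as repeat use, so first use came earlier. The first focus group on the interface comes one week after the initial visit, so the aid has been seen by then. Follow-up is counted from the baseline clinic visit, and no other initial visit is described. Because follow-up visits are optional, the first visit may be a patient's only exposure.

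**Step 2. Reproduce the plan's figure.** Inputs from Sample size and power analysis: 40% and 60%, 80% power, equal groups. The significance level of 0.05 is from Data analysis; the article does not state whether it is two-sided, but two-sided reproduces its figure. With the pooled formula and no continuity correction:

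n = [1.96 × √(2 × 0.5 × 0.5) + 0.8416 × √(0.4 × 0.6 + 0.6 × 0.4)]² / 0.20² = (1.3859 + 0.5831)² / 0.04 = 96.9, so 97 per group, as stated.

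The same formula gives 17 per group for 40% against 85%, also as stated. With 100 per arm, comparing 60% with 40% at a follow-up time has 81% power by normal approximation and 82.6% by exact enumeration of the chi-square test (80.7% at 97 per arm). This figure does not depend on when baseline values are recorded.

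**Step 3. What a change comparison would show.** Two inputs are not in the article and are assumed: f, the share of the 20-point effect already in the aid arm's baseline value, and ρ, the within-patient correlation between baseline and follow-up, taken as 0.3 to 0.7. Control stays at 40%; the aid arm is at 40% + 20f at baseline and 60% at follow-up.

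- Difference in change = 20 × (1 − f) points.
- With p = 0.4 + 0.2f, variance of change in the aid arm = p(1 − p) + 0.24 − 2ρ√[p(1 − p) × 0.24]; in control = 0.48 × (1 − ρ).
- Standard error = √[(sum of the two variances) / 100].

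Worked case, f = 0.5 and ρ = 0.5: p = 0.5, aid-arm variance 0.2451, control variance 0.24, standard error √(0.4851 / 100) = 0.0696. The ratio is 0.10 / 0.0696 = 1.44, which gives 30% power.

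| Share f in the baseline value | Difference in change | Power at ρ = 0.3 / 0.5 / 0.7 |
|---|---|---|
| 0 (recorded before the aid) | 20 points | 68% / 82% / 96%* |
| 0.5 | 10 points | 23% / 30% / 46% |
| 1 (whole effect immediate) | 0 points | 5% / 5% / 5% |

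*For a yes/no measure at 40% then 60%, the correlation cannot exceed (0.40 − 0.24) / 0.24 = 0.667. At that limit both variances are 0.16, the standard error is 0.0566 and power is 94%, so 96% is slightly out of reach.

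**Step 4. Which measures are exposed?** The 40% and 60% are rates of consistency with recommendations, which the change sentence does not list. The table therefore illustrates the mechanism and is not a power figure for a planned test. The mechanism reaches measures recorded during or after the first visit: orders placed there and surveys filled in afterwards. It does not reach medication already taken or imaging already obtained.

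**The case against.** The strongest reply is that the article never says baseline values are recorded after the aid is shown. Table 2 keeps pre-existing medication and recent imaging apart from what is ordered, so a reference from before the aid is already being collected for those measures. If that is what baseline means in the analysis, nothing is lost. This stands, and it makes the concern conditional.

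It can also be said that the change sentence names no reference visit and would fit a three-to-six-month change. That is possible. However, baseline is the earliest of the three visits listed just before it, and change starting there is the natural reading.

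A reader might infer something stronger: that the plan subtracts the very effect the trial is meant to measure, or that power for the main comparison drops from about 82% to 5%. The documents do not support this. The change analysis is additional. The primary endpoints are read at three and six months, and the success rule concerns levels: at least 85% of aid visits, with rates the same as or higher than control. Neither uses change from baseline. The 5% also requires the whole effect to be immediate, to be captured in the baseline value and to persist unchanged.

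Nor would a difference in level with no difference in change be a contradiction; they are different quantities. The problem is that the article does not say which value change starts from.

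Timing of recording could be called detail for a fuller document. But the article itself lists baseline as an outcome time and announces change between visits, so the two uses meet in its own text.

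**Conclusion.** The concern holds in conditional form. The first-use visit serves as an outcome time and as the earliest visit in a change analysis, while the sample-size section takes baseline to precede any effect of the aid. For measures recorded during or after that visit, the expected difference in change is 20 × (1 − f) points on the plan's own 20-point effect: 10 points if half is immediate, 0 if all is. The corresponding power is 23% to 46%, and 5%. These results rest on the assumed f and ρ, on the effect persisting, and on baseline values being recorded after exposure, which the article leaves open. The primary comparisons of levels, the success rule and the sample size of 97 per group are unaffected. The change is worth making because the additional analysis can mislead and a better one is nearly free.

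**What to change.** Under Data analysis:

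1. Define the baseline value as one obtained before the aid is shown. For medication and imaging, use the pre-existing and recently obtained entries in Table 2. For the Information Seeking and Sharing survey, give it before the aid is opened, at the same point of the visit in both arms.
2. Report orders placed and perceptions recorded at the first visit as post-aid outcomes, labelled separately from baseline.
3. Replace change from the baseline visit with between-arm comparisons at three and six months, adjusted for the pre-aid medication, imaging or survey value. The logistic regression now described covers survey questions only, adjusting for age, sex and education; extend it to the medication and imaging outcomes.
4. Some measures cannot have a pre-aid value, such as perceptions of decision-making in the visit itself. For these, describe any change only as change after first use.

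The adjustment should use the pre-aid medication and imaging status itself. A pre-visit score for consistency with recommendations would be a larger task, because consistency also counts recommendations offered and declined and may need adjudication.

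The cost is control of survey timing and a little more analysis. The sample size does not change.

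### Secondary survey questions and labs are each tested at P < 0.05 over several visits with no lead contrast, which puts the chance of at least one false positive well above 5%

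*Protocol article*

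**What the plan says.** All references are to the protocol article.

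- **Purpose.** Under Secondary endpoints: "Survey responses will be reviewed to determine the impact of the use of the clinical decision aid". The same section compares the percentages of favorable responses between arms. It expects at least 80% of questions to be scored favorably in the aid group, with scores no lower than in the control group. That expectation carries no P-value.
- **Unit of analysis.** Under Data analysis: "Scores will be calculated for individual survey questions, with a higher number indicating a more favorable response".
- **Tests.** Binary survey scores are compared by chi-square or Fisher's exact test. In addition, "Logistic regression will also be used to estimate the effect of the randomized group on the binary score for each survey question", adjusted for age, sex and, where known, education.
- **Visits.** Survey scores and labs are compared between arms "at single visits (baseline, three months, six months").
- **Change.** The plan adds that "changes over time in the Information Seeking and Sharing survey responses, imaging parameters, medication use, and lab tests if results applicable, will be investigated". Among the surveys, only this one is analysed for change.
- **Threshold.** "Statistical significance will be accepted as *P*-value of < 0.05". No order of testing, lead question, lead visit or adjustment accompanies it.
- **Consequence.** Age, sex and education are examined as predictors "for survey questions or short-term outcomes with results significantly different between the two randomized groups".
- **Labels.** The word exploratory is attached to the focus groups only (Focus groups; Exploratory endpoints).

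**The concern.** The survey endpoint is meant to show what the aid does to perceptions and health behavior. The analysis answers with a large set of separate tests, each judged at 5%, and does not say which one is to be believed if they disagree. A plan of this kind will often produce one or more significant questions or lab values when the aid has no effect. A report can then pick these out without departing from the plan.

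The one quantity that summarises the surveys, the aggregate benchmark, sits in a different section and is linked to none of the tests. A reader of the results would have two unconnected ways to judge the surveys and no statement of which carries the conclusion.

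This concerns the secondary survey and lab results. It does not concern the medication and imaging outcomes listed as primary in Table 2.

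**Working it through.** **1. Level of each test.** The article gives 0.05 but does not state the number of sides. Its own sample size settles the likely reading. For 40% v 60% with 80% power and a pooled variance under the null:

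n = [1.96·√(2·0.5·0.5) + 0.842·√(0.4·0.6 + 0.6·0.4)]² / 0.20² = [1.386 + 0.583]² / 0.04 ≈ 96.9, so 97 per group.

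This is the stated figure. A one-sided test would give 77. I therefore take two-sided 5% per test. The article states no error rate for the secondary tests, so there is no figure of that kind to reproduce.

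**2. Number of tests.** The number of survey questions is not given, so k is assumed. One count needs no assumption about questions. Secondary endpoints names five lab or body measures (troponin, NT-pro-BNP, potassium, lipid panel counted once, BMI). At three and six months that is 5 × 2 = 10 tests, provided the measures are available. As a further example, 20 assumed questions at the three listed visits make 60 tests. That count includes baseline, and the article does not fix whether the baseline survey comes before or after use of the aid.

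**3. Chance of at least one P < 0.05 with no true effect.**

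Independent tests: 1 − 0.95^k.
- k = 10: 1 − 0.5987 = 0.401
- k = 20: 1 − 0.3585 = 0.642
- k = 60: 1 − 0.0461 = 0.954

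Correlated tests: k equally correlated standard normal statistics, rejecting when |z| > 1.96, by simulation (50,000 runs). Numerical integration of the same model agrees to within half a percentage point.

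| k (assumed) | Independent | Correlation 0.5 | Correlation 0.8 |
|---|---|---|---|
| 10 | 40% | 28% | 17% |
| 20 | 64% | 42% | 23% |
| 60 | 95% | 67% | 31% |

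**4. Results favoring the aid only** (0.025 per test).

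| k (assumed) | Independent | Correlation 0.5 | Correlation 0.8 |
|---|---|---|---|
| 10 | 22% | 14% | 8% |
| 20 | 40% | 21% | 11% |
| 60 | 78% | 34% | 15% |

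Here the nominal rate for comparison is 2.5%.

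**5. Where the chance passes one half.** For independent tests in either direction, ln 0.5 / ln 0.95 ≈ 13.5, so from 14 tests. For results favoring the aid, ln 0.5 / ln 0.975 ≈ 27.4, so from 28 tests. At correlation 0.5, 30 tests in either direction give 51%. At correlation 0.8 even 60 tests give 31%.

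**6. Discreteness.** The exact size of one chi-square test with 100 patients per arm and an assumed 80% favorable in both is 0.051, so discreteness does not remove the inflation where chi-square is used.

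The unadjusted and adjusted analyses of one question are counted once here, because they are two looks at the same contrast.

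**The case against.** **The article is condensed and an analysis plan may exist.** Naming a key secondary endpoint and handling multiplicity are often left to it, and silence alone would be no finding. But the article is not silent. It fixes the question as the unit, lists the visits and sets one threshold for everything. A later plan would have to override that text. This objection lowers the weight of the point without removing it.

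**P < 0.05 is not the only yardstick.** This stands. The Secondary endpoints section has an aggregate benchmark, and the success definition under Primary endpoints asks for survey responses that are favorable overall. A reader might infer that one chance-significant question would count as success or settle the survey endpoint. The documents do not support that, because a single question satisfies neither criterion. What remains is that the benchmark is not linked to any of the planned tests.

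**The predictor step does no harm to the comparison.** This stands in part. A reader might infer that carrying significant questions forward manufactures further false effects of the aid. It cannot: that step examines age, sex and education as predictors and is not another test of randomized group. The fault is narrower. Chance findings decide which questions are modeled further.

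**This is a feasibility study and the outcomes are secondary.** True. The stated conclusions of the trial concern medication use and imaging. Labs are also conditional on being clinically indicated, so the number of lab tests may be smaller than listed.

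**Conclusion.** The point holds as an inexpensive improvement. As written, the plan tests every survey question and the labs at several visits, and one survey and the labs also on change, each at 5%, with no lead contrast and no descriptive label. The chance of at least one false positive is well above 5% in every case examined: 17% to 40% for 10 tests, 23% to 64% for 20 and 31% to 95% for 60. These figures rest on an assumed number of tests, an assumed common correlation between 0 and 0.8, two-sided 5% tests and no true effect.

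A reader might go further and conclude that a false claim of benefit is likely. The documents do not support that, because they give neither the number of questions nor their correlation. With strongly correlated items the chance stays below one half even at 60 tests, and results favoring the aid account for only part of it.

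**What to change.** In Secondary endpoints and Data analysis:

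1. Name one lead secondary contrast, built on the aggregate the article already describes: each patient's percentage of favorable survey responses, compared between arms at one named visit after the intervention, tested at 5%. The article already provides the t-test or Wilcoxon test for a continuous outcome. State which questions enter the percentage, and use only those put to both arms.
2. Report individual questions, other visits, change scores and labs as exploratory, with estimates and confidence intervals and no claim of significance.
3. Drop P < 0.05 as the rule that selects questions for the predictor analysis. List those questions in advance, or apply the analysis to the lead score.

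The OPTION5 score is a poor choice of lead. It depends on visit recordings that the article says only may be made, and it measures shared decision-making, whereas the secondary endpoint concerns perceptions and behaviors.

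The cost is a wording change, with no new patients or data. The downside is that single-question results lose their claim to significance.
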